## Abstract

**Background:**

Maternal and perinatal mortality are major problems for which progress in sub-Saharan Africa has been inadequate, even though childbirth services are available, even in the poorest countries. Reducing them is the aim of two of the main Millennium Development Goals. Many initiatives have been undertaken to remedy this situation, such as the Advances in Labour and Risk Management (ALARM) International Program, whose purpose is to improve the quality of obstetric services in low-income countries. However, few interventions have been evaluated, in this context, using rigorous methods for analyzing effectiveness in terms of health outcomes. The objective of this trial is to evaluate the effectiveness of the ALARM International Program (AIP) in reducing maternal mortality in referral hospitals in Senegal and Mali. Secondary goals include evaluation of the relationships between effectiveness and resource availability, service organization, medical practices, and satisfaction among health personnel.

**Methods/Design:**

This is an international, multi-centre, controlled cluster-randomized trial of a complex intervention. The intervention is based on the concept of evidence-based practice and on a combination of two approaches aimed at improving the performance of health personnel: 1) Educational outreach visits; and 2) the implementation of facility-based maternal death reviews.

The unit of intervention is the public health facility equipped with a functional operating room. On the basis of consent provided by hospital authorities, 46 centres out of 49 eligible were selected in Mali and Senegal. Using randomization stratified by country and by level of care, 23 centres will be allocated to the intervention group and 23 to the control group. The intervention will last two years. It will be preceded by a pre-intervention one-year period for baseline data collection. A continuous clinical data collection system has been set up in all participating centres. This, along with the inventory of resources and the satisfaction surveys administered to the health personnel, will allow us to measure results before, during, and after the intervention. The overall rate of maternal mortality measured in hospitals during the post-intervention period (Year 4) is the primary outcome. The evaluation will also include cost-effectiveness.

**Trial Registration:**

The QUARITE trial is registered on the Current Controlled Trials website under the number ISRCTN46950658 .

## Background

### Maternal and perinatal mortality in sub-Saharan Africa

In sub-Saharan Africa, maternal and perinatal mortality and morbidity are major problems for which progress has been inadequate. Reducing them is the aim of two of the Millennium Development Goals (MDG4 and MDG5) whose attainment in this region of the world is very unlikely [1]. The broad strategies that have made it possible to reduce maternal and perinatal mortality are known: prenatal care, labour and delivery management by qualified personnel, and availability of emergency obstetric care (EmOC) [2]; however, their implementation is a major challenge in sub-Saharan Africa, where healthcare systems are fragile and still being developed. Service availability and quality of care in health facilities are very heterogeneous and most often inadequate [3-7]. According to WHO, it will be important, over the next 10 years, to update the skills of many professionals who do not currently have the competencies required to provide EmOC [8]. In addition, among the trained professionals currently on staff, it is apparently difficult to maintain a high level of performance in services that are often disorganized and under-equipped [9]. The lack of motivation leads to a high level of staff turnover, with responsibilities then falling on categories of staff that are less qualified [10].

In Mali and Senegal, the rates of maternal mortality estimated by WHO in 2005 remain high: 970 and 980 maternal deaths per 100,000 live births, respectively [8]. Emergency obstetric care coverage is poor (around 15%) [5,7]. On the other hand, according to UN indicators, there are enough referral centres equipped with functional operating rooms. However, the quality of care in the referral centres is inadequate, as evidenced by high case fatality rates (above 1%) [5,7].

### Interventions to improve the performance of health professionals

The concept and techniques of continuous quality improvement offer a variety of strategies to improve the performance of health professionals [11]. These approaches relate to complex interventions in which health professionals are directly involved in analyzing and modifying care processes to improve their performance and the health outcomes of their patients.

A meta-analysis of educational outreach visits, including 69 randomized controlled trials, most of which were carried out in industrialized countries, shows moderate effects in terms of changing professional practices, with considerable heterogeneity depending on professional categories and contexts [12].

A meta-analysis of audit and feedback approaches that reviewed 47 randomized controlled trials with more than 3,500 clinicians shows that this technique may be effective in improving medical practices. The baseline compliance with recommended practice (prior to intervention) and the intensity of audit and feedback are major factors influencing the effectiveness of this technique [13].

In low-income countries, a systematic review of interventions aimed at improving the performance of health professionals suggests that: (i) simple dissemination of written guidelines is often ineffective, (ii) supervision and audit with feedback are generally effective, and (iii) multifaceted interventions might be more effective than single interventions [9].

The ALARM (Advances in Labour and Risk Management) International Program, or AIP, was developed by the Society of Obstetricians and Gynaecologists of Canada (SOGC). It is based on a combination of two potentially effective approaches for improving performance among health professionals [14]: 1) educational clinically-oriented and evidence-based outreach visits focused on the principal causes of maternal mortality, and 2) facility-based maternal death reviews or audits, as proposed by WHO [15]. In 2005, we conducted a pilot study in Senegal to analyze the feasibility of maternal death reviews in five referral hospitals [16]. The results of this study confirm that the majority (87%) of maternal deaths in referral hospitals are attributable to direct obstetric causes, and three-quarters of these can be avoided using locally-adapted measures. The results also suggest that the involvement and leadership of those in charge of maternity services (physician and midwife) play a primordial role in implementing audits. The capacity of those in charge of the service to ensure such leadership depends on the following key aptitudes: (i) knowledge of evidence-based practice for the main obstetric complications; (ii) an understanding of non-medical reasons for maternal death (social, economic, cultural, and legal dimensions of maternal mortality); and (iii) a mastery of the clinical audit approach. We also showed, in another study carried out in a district hospital in Senegal, that the routine conduct of maternal death audits led to a reduction in maternal mortality of 50% in year 3, in comparison with the pre-intervention period [17].

### What is not known

While the results of some observational studies carried out in sub-Saharan Africa are promising enough [17-19], we have no evidence regarding the effectiveness, in terms of reducing maternal and perinatal mortality, of interventions based on educational outreach visits and audits, nor on their large-scale implementation. For reasons of cost and availability of information, studies on maternal and perinatal health interventions in developing countries are based preferentially on process indicators rather than health outcomes indicators [3-7].

From our pilot study in Senegal, the following questions emerged: 1) Does the AIP promote the development of local leadership? 2) Does the AIP produce changes in clinical practice among the health professionals? 3) Do the changes in practice have an effect, in the medium term, on maternal and perinatal mortality? 4) Does the AIP have an effect on staff satisfaction? 5) Can the intervention model be modified to improve cost-effectiveness? The QUARITE trial is an attempt to respond to these questions and to the need for more evidence on the effectiveness and functioning of interventions aimed at reducing maternal and perinatal mortality and morbidity in developing countries.

### Hypotheses

Our hypothesis is that the ALARM International Program (AIP) reduces the overall rate of maternal mortality, as measured in the hospitals in the post-intervention period, by 30% in comparison with the control group. Secondary hypotheses are that the AIP: 1) reduces the number of stillbirths and early neonatal mortality; 2) reduces severe maternal morbidity and the case fatality rate; 3) improves the quality of care through better utilization of local resources and changes in professional practices; and 4) increases the satisfaction of health professionals.

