### Intervention group activities

These activities started in September 2008 and will end in August 2010. Professionals from the intervention group have been trained in evidence-based practice using the ALARM international course [14] that targets health professionals who provide obstetrical care, reviewing the top maternal killers and suggesting essential tools and problem management with the goal of improving care for mothers and newborns. This course promotes evidence-based practice, using data from up-to-date systematic reviews of randomized trials. The course was developed and is maintained and taught jointly by family physicians, obstetricians, midwives, and nurses from developing countries. It has the administrative support and backing of the SOGC.

The sequence of activities during the two years is directed toward developing local leadership and empowering obstetric teams. To meet this objective, the intervention will be carried out in several steps (Figure 1). The intervention began with recruitment of opinion leaders in each centre and their training in best practices and in maternal death audits (training the trainers). The opinion leaders will then create, in their own centres, obstetric teams charged with implementing the maternal death audits and will organize staff training in best practices with the support of external facilitators (educational outreach visits).

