***c) Maternal and perinatal health outcomes***: The incidence of maternal mortality will be measured, as well as its distribution among its principal causes: pre- and postpartum hemorrhage, prolonged or dystocic labour, uterine rupture, postpartum infection, pre-eclampsia/eclampsia. We will also measure, in each facility, the case fatality rate, the rate of stillbirths, and early neonatal mortality (during hospitalization). We will monitor referrals in and out of the facilities and track the mortality of mothers and babies discharged from the institutions, using the existing information systems (hospital registers and feedback from referral institutions to the others) and calling the institutions when the information is not available.

Audit of maternal deaths is the cornerstone of this complex intervention. According to WHO [15], audit of maternal deaths should improve inter-personnel communication, team working (and staff motivation), resource availability, performance of health workers, and quality of care. Training for the local opinion leaders and parallel training for other staff in best practices should reinforce the effects of the audit activities on health workers' performance. The other components of the intervention should facilitate the implementation of the program using activities to support the actors (outreach visits). As with other complex interventions, the synergy among all components is expected to be effective. All these effects will ultimately have an impact on maternal mortality (see Figure 3). The effects of each component will be assessed by measuring the process indicators: indicators for the implementation of the program, and indicators of resource availability and of quality of care.

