### Data collection and management

#### Data collection

A system of data collection, independent of the AIP, was set up in September 2007 in the 46 study hospitals. This system is based on the WHO global survey on maternal and perinatal health [20], which considers clinical data at the individual level and organizational data at the facility level. All deliveries carried out in the participating centres are registered by local collectors (nurses or midwives trained to do this). These collectors complete a standard form for each eligible patient that includes information on maternal characteristics, prenatal care, labour and delivery, diagnosed complications, and the vital status of both mother and child at discharge from hospital (see patient registration form, Additional file 1). This information is extracted from the hospital registers and from available medical records whose quality and archiving are regularly monitored by the national coordinator of the study. These data will be collected on an ongoing basis throughout the study. With respect to facility-level data, the national coordinator carries out an annual inventory of the resources available in each hospital using a standardized grid, by visiting all the services of the hospitals involved in EmOC.

To assess the quality of care, we will sample medical records of 50 patients at each of the 46 participating centres using simple random sampling. An external evaluator will assess each record using a criterion-based clinical audit (CBCA) to obtain a score for quality of care. The CBCA scores, ranging from 0 to 27, are then dichotomized as standard (score equal to or greater than 22) versus sub-standard (score below 22) care. The sample size of 50 records/centre will allow us to estimate the proportion of patients receiving standard care in each centre with sufficient precision. Specifically, the half-width of the 95% confidence interval will not exceed 15%. The CBCA developed by the researchers of the QUARITE trial employs evidence-based clinical criteria to ascertain if minimal quality of care is provided to the patients sampled. These criteria have been selected based on thorough review of the literature and expert consensus and are consistent with the WHO guidelines for conducting an obstetrical CBCA (Beyond the numbers: Reviewing maternal deaths and complications to make pregnancy safer. Geneva: World Health Organization, 2004) [15].

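### A fall in case fatality could come from better recording of complications in the intervention arm alone, so it should not count as benefit without the recorded incidence beside it

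*Protocol article*

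**What the plan says.** All references are to the protocol article.

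- **Hypotheses.** The second secondary hypothesis is that the programme "reduces severe maternal morbidity and the case fatality rate".
- **Study endpoints.** "We will also measure, in each facility, the case fatality rate". The denominator is not defined there, and severe maternal morbidity is not named in the endpoint list.
- **Data collection.** Deliveries are "registered by local collectors (nurses or midwives trained to do this"). The form covers, among other items, "diagnosed complications, and the vital status of both mother and child at discharge from hospital". On its source: "This information is extracted from the hospital registers and from available medical records".
- **Intervention group activities.** Intervention staff take a course "reviewing the top maternal killers and suggesting essential tools and problem management", followed by local training sessions and quarterly outreach visits. Under Control group, no external intervention is planned.
- **Quality control of data.** Forms are counted against the birth register, completion is checked on four items (entry date, identification, discharge date, mother's vital status), and forms are compared with registers and records. Additional case-finding applies to maternal deaths.
- **Statistical analyses.** Secondary criteria are analysed by the same GEE approach as the primary, with one-tailed Wald tests at 0.05.

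**The concern.** Case fatality is a ratio, and the intervention can act on both parts of it. The intended route is fewer deaths. The unintended route is more recorded cases: staff taught about haemorrhage, pre-eclampsia and infection may recognise and write down cases that they would previously have missed. Added non-fatal cases enlarge the denominator and lower the rate, although no woman is better off.

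The training is confined to one arm, so the shift would be a difference between arms and not a common trend. The Background section already reads a high case fatality rate as a sign of inadequate care, so a fall would naturally be read as improvement. At stake is a secondary conclusion that would appear to support the programme's mechanism and might carry particular weight if the mortality result were unclear.

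**Working it through.** **1. The plan's own figure.** The article gives no expected value, target or power for case fatality as a trial outcome. Its one power figure concerns maternal mortality: 82% with 38,205 women. It reproduces. With 1.5% against 1.055% (odds ratio 0.70), design effect 1 + 829 × 0.001 = 1.829 and 38,205 / 2 / 1.829 = 10,444 effective women per arm, two-sided power is 0.817. Nothing below depends on it.

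**2. Can the stated checks see the problem?**
- Counting forms against the birth register finds missing women, not missing diagnoses.
- The completion items do not include complications.
- Concordance compares the form with the record. A complication never diagnosed is absent from both, so they agree.
- The search across admission, ward, operating-room and morgue registers finds deaths only.
- The baseline year measures recording before training. A shift that starts with the training, in one arm, is not removed by adjusting for it.
- The limitations section considers a data-collection effect taken as equal in both arms, and staff transfers. It does not consider a change in diagnosis.

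**3. Size of the artefact.** Case fatality = deaths / recorded cases. Hold deaths fixed and multiply recorded cases by k. The relative fall is 1 − 1/k. The values of k are assumptions, because the article gives no figure.

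| Rise in recorded cases | k | Fall in case fatality |
|---|---|---|
| 10% | 1.1 | 1 − 1/1.1 = 9.1% |
| 20% | 1.2 | 1 − 1/1.2 = 16.7% |
| 30% | 1.3 | 1 − 1/1.3 = 23.1% |

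This result does not depend on the level of case fatality.

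**4. What a test might do with it (illustration under no true effect).**
- From the article: 96,941 expected deliveries, so 48,470.5 per arm if split equally; mortality 1.5%, here applied to both arms; intra-cluster correlation 0.001.
- Assumed: every death is a recorded case; true complications are 10% or 20% of deliveries; control staff record 60% or 80% of non-fatal ones; intervention staff record 10 percentage points more.

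Example with 10% complications and 60% recorded by control staff:
- Deaths per arm: 48,470.5 × 0.015 = 727.
- Control cases: 48,470.5 × (0.015 + 0.085 × 0.60) = 3,199. Case fatality 727 / 3,199 = 22.7%.
- Intervention cases: 48,470.5 × (0.015 + 0.085 × 0.70) = 3,611. Case fatality 727 / 3,611 = 20.1%.
- Ratio 0.89.

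Over the four combinations the ratio runs from 0.87 to 0.91. The design effect is 1 + (control cases per hospital − 1) × the intra-cluster correlation. By normal approximation, a one-sided 5% test in the direction of a fall would then declare a reduction 58% to 79% of the time. At an assumed intra-cluster correlation of 0.01 the figure is 27% to 52%. The nominal rate is 5%. The correlation for case fatality is not given; 0.001 is the article's value for maternal mortality.

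**The case against.** **The link is inferred.** The article says that the course covers the main causes of death and their management. It does not say that the course changes recognition or recording. That stands, and it is why the size is shown as a range.

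**The data system is separate.** "A system of data collection, independent of the AIP, was set up in September 2007". This concerns who collects the data. The collectors still copy diagnoses made by clinical staff, so separation does not protect the denominator.

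**The definition may lie elsewhere.** The patient form and the full protocol are not shown. If cases for case fatality are defined there by events that cannot be overlooked, the concern shrinks. This also stands. The missing definition is not itself the finding.

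**Stronger readings that the article does not support.**
- A reader might infer that recorded severe morbidity must rise and that the second secondary hypothesis therefore cannot be answered at all. Severe morbidity has no definition here, and newly recognised milder cases need not enter a severe category. Any such bias would also run against the hypothesised reduction: it could hide a benefit but not create one.
- A reader might set the 23% beside the 30% effect that the trial is designed for. That 30% is the target for maternal mortality; none is given for case fatality.
- A reader might want cause-specific deaths as the tested replacement. Death audits are introduced as part of the intervention, so attribution of cause could also shift by arm, and the measure only subdivides the primary endpoint. Hysterectomy is no safe substitute for morbidity either, because the article lists it among the interventions that indicate quality of care.

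**Conclusion.** The point holds for case fatality as an interpretive weakness of one secondary endpoint. On the sources stated, its denominator can be moved by the intervention in one arm only, and no described check would show it. The fall is 9% to 23% for an assumed 10% to 30% rise in recorded cases with deaths unchanged. The false-positive figures are illustrative and depend on assumed complication frequency, recording rates and clustering. Three things carry the conclusion: that cases are taken from diagnosed complications, that training raises recognition or recording, and that the cases gained are non-fatal.

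The primary endpoint, maternal deaths among women giving birth in the facility, does not use diagnosed complications and is not exposed to this mechanism. For severe morbidity no conclusion can be drawn from this document.

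**What to change.** - Report case fatality only beside the recorded incidence of each complication, by arm and by study year.
- State before the data are analysed that lower case fatality together with higher recorded incidence in the intervention arm is not evidence of benefit.
- Read case fatality with maternal deaths per all deliveries, whose denominator does not depend on diagnosis. Use the total, with the cause distribution already planned under Study endpoints as descriptive support.

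This is a change of wording and one extra table, from complications already on the patient form. The downside is that case fatality carries less weight as evidence on its own, and a real fall that coincides with better recognition could not be claimed from it alone.

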### Aims

The objective is to evaluate the effectiveness of the AIP in reducing maternal mortality at referral hospitals in Mali and Senegal, as well as improvements in perinatal health, resource availability, service organization, medical practices, and the satisfaction of health personnel.

